### Aims 3 and 4: Evaluate the Preliminary Effectiveness of Tele-BE in Engaging Target Mechanisms and Enhancing Clinician Fidelity to CBT

#### Overview

Although aims 3 and 4 are scientifically distinct, study procedures will occur concurrently and are described together. We will randomize 30 clinicians who already provide individual CBT via telehealth for at least 2 clients to either Tele-BE or telehealth as usual (Tele-AU), with 15 clinicians per condition. Allocation will be balanced within organizations to ensure equal representation across conditions within each agency. Each participating clinician will deliver treatment to 2 patients over 12 weeks, the standard length for many CBT protocols, and clinician fidelity to CBT structural components will be tracked in each condition. While the primary goal is to evaluate the feasibility of our design and measurement approach for a fully powered trial, we will also measure patient symptoms, therapeutic alliance, and patient-centered care to explore preliminary clinical effectiveness outcomes and assess any potential concerns with Tele-BE (eg, clinician distraction or impact on therapeutic alliance) using mixed methods.

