#### Quantitative Measures: Aim 3 Primary Outcomes

The primary outcome for aim 3 is clinician fidelity to structural components of CBT. We will code all recorded therapy sessions (up to 720 sessions: 60 patients × 12 sessions) for the presence of 6 structural components: (1) discussion or review of patient symptoms, (2) homework review, (3) agenda setting, (4) skill instruction or review, (5) skill practice, and (6) out-of-session practice (homework). Coding will use items from the CTRS, a gold-standard CBT fidelity measure with 11 observer-rated items, including those indexing the specific structural components of interest (homework review and planning, agenda setting, skill instruction, and skill practice) [60]. Each CTRS item is scored on a 7-point Likert scale ranging from 0 (poor) to 6 (excellent), allowing fidelity to be defined in 2 ways: (1) the presence or absence of each component, and (2) whether each component meets a competency threshold (ie, a score of 4 or higher). Our primary focus will be on the presence/absence of each component, calculated as the sum of the binary outcomes. Presence above the competency threshold will serve as a secondary outcome. The CTRS demonstrates strong internal consistency and interrater reliability [60], as well as strong interrater agreement for general competency [32]. Importantly, the CTRS includes a subscale assessing structural competency [31], in addition to scores for specific structural components and an overall competency score.

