Given the volume of recorded sessions, CTRS scores will be generated for each session using the Lyssn platform. Lyssn [61] (pronounced “listen”) is a technology start-up that employs artificial intelligence (AI) to support training, supervision, and quality assurance of EBPs. Lyssn’s cloud-based platform provides the following: (1) user management and organization of sessions, clinicians, and supervisors; (2) recording, playback, and annotation of audio or video from therapy sessions; (3) speech-to-text transcription; (4) AI-generated fidelity and quality metrics; and (5) data summaries and visualizations for feedback. Session recordings are automatically transcribed using Lyssn’s speech recognition algorithms, which were trained on over 4000 sessions [62-64]. Using transformer-based deep neural networks [65], Lyssn developed AI-generated models for the 11 CTRS codes, trained on 2494 sessions with corresponding CTRS ratings within a cross-validation framework of training and test partitions [66,67]. Evaluation on a 30% test set of sessions, distinct from the training data, demonstrated strong predictive performance. For all but 1 code (*Understanding*, which is not a structural component of interest in this study), AI-generated predictions exceeded the 80% human reliability threshold. Using AI-generated metrics, the tools achieved 100% human-level reliability for total CTRS scores and demonstrated highly accurate reliability for individual items. Lyssn maintains an in-house coding team that continuously provides new validation and calibration data to monitor and sustain the performance of the AI algorithms.

While CTRS scores will serve as our primary fidelity metric, we will also examine self-reported fidelity to CBT structural components within the Tele-BE condition using web analytics data collected through the platform. As clinicians engage with Tele-BE, they will check off each structural component as it is completed in session or indicate if they intentionally override a component (Figure 1). This will provide self-reported data on structural component use for every recorded patient session in the Tele-BE condition. These data will allow comparison between self-reported use and Lyssn-generated CTRS scores, and provide insights into how and when clinicians override the Tele-BE infrastructure, informing aim 4 assessments of acceptability.

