#### Quantitative Analyses

Aim 3 primary analyses will focus on structural component scores from the CTRS generated via the Lyssn platform, dichotomized as present or absent. An aggregate fidelity metric will be calculated for each session by summing the number of components present. We will use a linear mixed effects regression model to estimate the trajectory of completion scores over the 12 weeks of treatment. Fixed effects will include linear and quadratic time trends to capture the overall trajectory, although more flexible specifications will be considered if needed. To account for correlations arising from patients nested within clinicians, a random intercept for clinicians will be included, along with correlated residuals to address within-patient correlations over time. The model will use data from all 12 sessions to estimate time trends, as well as session means and standard errors for each session. Additionally, monthly estimates will be generated to align with participant survey intervals. As described above, we will also create an overall structural component sum score for each session by summing the total structural components rated as “completed at or above the satisfactory threshold” on the CTRS. If sufficient variability exists, we will model the time course using mixed effects models as described previously. If the score range is too narrow, we will use mixed effects ordinal regression models, with fixed and random effects specified similarly. All analyses will include patient demographics (eg, age, diagnosis) as covariates. In addition to CTRS-based fidelity measures, self-reported fidelity will be captured for the intervention group using web analytics data. The primary self-report measure will parallel the CTRS, summing the number of structural components rated as present. We will use a bivariate-response mixed effects model, treating CTRS and web-based measures as concurrent responses across the 12 weeks, to compare overall levels and trends over time between the 2 measurement methods.

To examine secondary outcomes (intentions and determinants of intentions), we will model monthly trends in clinician-reported intentions, attitudes, self-efficacy, and perceived social norms using approaches analogous to those described for fidelity measures. The primary distinction is that time will be treated as a categorical variable, reflecting the 3 assessment points rather than the 12 weekly sessions.

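### The planned comparison of Tele-BE check-offs with CTRS tests the level and trend of session sums, which shows net over- or under-reporting but not whether a checked component was delivered

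*Protocol article*

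**What the plan says.** The Overview of Aims 3 and 4 randomizes clinicians "with 15 clinicians per condition", and adds: "Each participating clinician will deliver treatment to 2 patients over 12 weeks". Under Quantitative Measures: Aim 3 Primary Outcomes, recordings are coded ("up to 720 sessions: 60 patients × 12 sessions") "for the presence of 6 structural components". In the Tele-BE arm the clinician also checks off each component in the platform, or marks it as deliberately overridden. The section gives the purpose: "These data will allow comparison between self-reported use and Lyssn-generated CTRS scores".

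Quantitative Analyses states how the comparison is made. It says that "self-reported fidelity will be captured for the intervention group using web analytics data", and that the main self-report measure parallels the CTRS measure by "summing the number of structural components rated as present". Both sums enter one bivariate mixed model, used "to compare overall levels and trends over time between the 2 measurement methods". No other quantitative comparison of the two sources is described, and no significance level is given for this one.

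**The concern.** Whether a check-off can be trusted is a paired question: was this component, checked in this session, found in the recording of this session? The level and trend of the sums answer a different question, namely whether clinicians claim more or fewer components on average than the CTRS finds. A false check for agenda setting and a missed click for homework cancel in the sum, although both are errors.

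The answer matters for the platform. Table 1 builds checkmarks, badges and congratulatory notices around completed components, and the clinician interviews use the self-reported data to ask how nudges were followed or overridden. Table 2 lists web analytics beside the CTRS for structural component fidelity. Clicks move the display on and can earn rewards, so clicking without delivering is plausible. The data needed to detect it are already collected.

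**Working it through.** **Counts.** The plan gives no power, error rate or agreement threshold for this comparison, so there is no such figure to reproduce. Its session count does reproduce: 60 × 12 = 720, of which 15 × 2 × 12 = 360 are in Tele-BE. With the 20% clinician dropout in Missing Data Considerations, 12 clinicians and 12 × 24 = 288 sessions remain. At 6 components each, that is 2,160 or 1,728 paired check-off/CTRS observations.

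**What the contrast measures.** Per session, let FP be the number of components checked but not CTRS-present, and FN the number CTRS-present but not checked. Then

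- difference in sums = FP − FN;
- proportion of components in disagreement = (FP + FN) / 6.

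The level contrast is the mean of FP − FN, and the trend contrast is its change over weeks. Neither depends on FP + FN.

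**Example.** Assume a mean CTRS sum of 3.6 of 6, a rate of 0.6 per component. Unrelated check-offs at the same rate give FP = FN = 6 × 0.6 × 0.4 = 1.44, so the difference is 0. Yet 2.88 of 6 components disagree, and agreement is 0.6² + 0.4² = 52%, which is chance level (kappa 0).

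**Simulation.** From the protocol: 15 (or 12) clinicians, 2 patients, 12 sessions, 6 binary components. Assumed: clinician SD 0.8 and session SD 0.7 on the logit scale, mean CTRS sum about 3.6, two-sided 5% level. Level and trend of check-off minus CTRS were tested on clinician summaries (t tests), and jointly by Hotelling's T². There were 4,000 runs per equal-mean setting and 2,000 otherwise. For tracking check-offs, each shares the component's underlying draw with probability 0.8.

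Equal means and trends, 15 clinicians:

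| Check-offs | Non-significant: level / trend / joint | Kappa | Raw agreement | Within-clinician session correlation |
|---|---|---|---|---|
| Unrelated to delivery | 94.8 / 95.3 / 94.6% | 0.00 | 52% | 0.00 |
| Match the clinician's average only | 95.0 / 95.8 / 95.1% | 0.10 | 57% | 0.00 |
| Track delivery | 94.6 / 95.5 / 95.1% | 0.84 | 92% | 0.88 |

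With 12 clinicians, unrelated check-offs give 94.9 / 95.2 / 95.3% and tracking ones 95.3 / 95.6 / 95.3%. If level and trend are tested separately, both are non-significant about 0.95² = 90% of the time. A random-intercept mixed model on the session differences (unrelated, equal means, 15 clinicians, 300 runs, z/Wald tests) gave 92–93%.

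**Unrelated check-offs with a higher mean.** The excess is the check-off mean minus 3.60 (3.89, 4.16, 4.65, 5.04).

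| Excess, components per session | Level non-significant, 15 clinicians | 12 clinicians |
|---|---|---|
| 0.29 | 89% | 89% |
| 0.56 | 68% | 74% |
| 1.05 | 14% | 26% |
| 1.44 | 0.7% | 2% |

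**Tracking check-offs 0.56 too high.** Kappa is 0.67 and raw agreement 85%, yet the level test was significant in essentially all runs. Here FP + FN = 6 × 0.15 = 0.90 and FP − FN = 0.56, so FP = 0.73 and FN = 0.17. The confirmed share of check-offs is (4.16 − 0.73) / 4.16 = 82%, and the share of delivered components checked is (3.60 − 0.17) / 3.60 = 95%. In the unrelated, equal-mean case both shares are only 60%, the base rate, and the test is usually silent.

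**The case against.** A reader might infer that unrelated check-offs would go unnoticed about 95% of the time. The documents do not support that in general. The 95% is 1 minus an assumed 5% level and holds only when the two means and trends coincide. Unrelated check-offs that run about one component high are detected in 86% of runs with 15 clinicians and 74% with 12. Nor did the simulation fit the planned bivariate model: it tested the same level and trend contrasts on differences. The bivariate model can estimate a session-level correlation between the two responses, which would separate the extreme cases. So pairing is not wholly lost at session level. Two facts remain: the article does not say this correlation will be reported, and a correlation of sums cannot show which component was misreported.

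A reader might also infer that a null result will be taken to validate self-report. No section says so. The CTRS is named as the main fidelity measure, and Progression Criteria uses AIM and FIM scores, CTRS-measured component use and qualitative evidence on motivation, not check-offs as a fidelity criterion.

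Finally, a level contrast is a sensible way to look for over-reporting, the two sections do not contradict each other, and agreement indices are often left to an analysis plan. All of that stands. The absence of a named kappa is not the point. The point is that the one contrast the article states cannot show whether check-offs match delivery.

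**Conclusion.** The concern holds in a limited form. The stated contrast addresses net over- or under-reporting, not agreement. When levels and trends coincide, it is non-significant about 95% of the time whether check-offs track delivery or are unrelated to it. Conversely, check-offs that track delivery well but run slightly high are declared different. Neither a null nor a significant result therefore shows whether a check-off reflects delivery.

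The cancellation in the sums is algebraic and needs no simulation. The 95% rests on the assumed two-sided 5% level and equal means and trends; the detection rates under unequal means also depend on the assumed SDs and the mean of 3.6. The consequence is modest: this is a secondary analysis in the Tele-BE arm only, and it affects neither the between-arm CTRS comparison nor the progression criteria. The change is still worth making, because it uses data already collected.

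**What to change.** Keep the bivariate model for level and trend, describe it as a check for over- or under-reporting, and report its within-clinician, session-level cross-response correlation. Add a paired analysis over every session and component with both sources:

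- the proportion of check-offs confirmed by the CTRS;
- the proportion of CTRS-present components that were checked off;
- kappa, by component and pooled.

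Give clinician-clustered intervals, and show components marked as intentional overrides separately. State that equal levels alone will not be read as agreement.

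The cost is a few lines of text and a little extra analysis, with no new data. Intervals from about 12–15 clinicians will be wide, so the results should be presented as estimates rather than as a pass/fail test.

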**Methods:**

We will refine the Tele-BE prototype in collaboration with clinicians and supervisors, who are the target end users (aim 1). Working closely with our web development team, we will field test and iteratively refine Tele-BE using rapid-cycle prototyping to optimize user experience and fine-tune the BE strategies (aim 2). The revised platform will then be evaluated in a 12-week open trial involving 30 community mental health clinicians, who will be randomized to either Tele-BE or telehealth as usual. Each clinician will deliver treatment to 2 patients, resulting in a total of 60 patient participants. All sessions will be recorded and coded to assess CBT fidelity. Clinicians and patients will complete questionnaires at weeks 1, 5, 9, and 12, with qualitative interviews conducted at the end of the trial. Primary outcomes will focus on fidelity to CBT structural components, measured via coding of recorded sessions. Secondary outcomes will include target implementation mechanisms—intentions and their determinants (attitudes, norms, and self-efficacy)—assessed using mixed methods, as well as overall CBT fidelity (aim 3). Additionally, trial data will be used to evaluate the acceptability and feasibility of Tele-BE from both patient and clinician perspectives, along with any potential ethical concerns associated with its use (aim 4).

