##### Participants and Procedures

We will identify at least 4 local agencies that use telehealth and have participated in system-sponsored BCI CBT training [55] as recruitment sites. A cascaded recruitment strategy, previously successful in other studies, will be employed to recruit 30 CBT-trained clinicians who treat study-eligible patients (ie, age 14 or older, consistent with the local age of consent for mental health services; already deemed appropriate for CBT; and already using telehealth as their preferred therapy modality). In this approach, clinicians will then help select 2 patients with whom they plan to use CBT and will approach those patients about participating in the study. If a clinician has more than 2 patients with whom they plan to use CBT, 2 patients will be randomly selected from the larger pool for study participation. After obtaining informed consent, clinicians will be randomized to either the Tele-BE or Tele-AU condition. Study procedures will be identical across conditions, with the only difference being that clinicians in the Tele-BE condition will use the new telehealth tool, while those in the Tele-AU condition will use the telehealth methods established by their organization. All sessions will be video-recorded using encrypted, HIPAA-compliant technology via the clinicians’ assigned telehealth platform. Clinicians and patients will complete questionnaires at 4 time points—baseline/week 1, week 5, week 9, and week 12—and participate in a qualitative interview posttrial (Table 2).

Clinicians will receive US $150 for completing study measures (US $50 for week 1 and posttrial, US $25 for weeks 5 and 9). Patients will receive US $5 per session for providing brief self-report data and allowing their sessions to be recorded, for a maximum of US $60; those completing qualitative interviews will receive an additional US $25. Clinicians and patients in both conditions will follow the same study activity schedule and complete the same assessment battery, except that participants in the Tele-BE condition will also respond to condition-specific qualitative interview questions. Compensation rates are consistent with our prior work.

**Table 2 table2:** Trial assessment schedule for aims 3 and 4.

Outcomes		Measures	Tele-BE^a^																										Post
				1		2		3		4		5		6		7		8		9		10		11		12			

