**Aim 3 secondary outcomes**																													
	Clinician intentions	Established stems [57]	✓		N/A		N/A		N/A		✓		N/A		N/A		N/A		✓		N/A		N/A		N/A		✓		
	Clinician attitudes	Established stems [57]	✓		N/A		N/A		N/A		✓		N/A		N/A		N/A		✓		N/A		N/A		N/A		✓		
	Clinician norms	Established stems [57]	✓		N/A		N/A		N/A		✓		N/A		N/A		N/A		✓		N/A		N/A		N/A		✓		
	Clinician self-efficacy	Established stems [57]	✓		N/A		N/A		N/A		✓		N/A		N/A		N/A		✓		N/A		N/A		N/A		✓		

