#### Quantitative Measures: Aim 3 Secondary Outcomes

Secondary outcomes are the target implementation mechanisms that align with our theorized mechanisms of action: intentions to use structural components of CBT and determinants of those intentions (Table 1). We will measure the strength of intentions separately for each structural component using established item stems from social psychology, designed to be adaptable to any behavior of interest [68]. Intentions will be assessed with 2 items on a 7-point scale, asking how willing and how likely a clinician is to use each component, with higher scores indicating stronger intentions. The 2 items will be averaged for each component. Determinants of intentions will be assessed through attitudes toward each component, measured with 4 standard semantic differential scales [40,69] (eg, 7-point scales ranging from “extremely unpleasant” to “extremely pleasant” or “extremely wise” to “extremely foolish”). Total scale scores will be computed by averaging all *z*-standardized items within each structural component, with higher scores indicating more favorable attitudes. *Norms* will be assessed using 2 standard item stems: the perception that “other people like me” will use the component, and that important others (eg, supervisors) will approve of their use, rated on a 7-point agreement scale. *Self-efficacy* will be measured with 3 statements on a 7-point scale assessing clinicians’ perceived ability to perform each component (eg, agreement with “If I really wanted to, I could use an agenda”). All items will be asked separately for each structural component and aggregated for the primary analysis, with exploratory analyses examining variation by component.

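### The mechanism model counts 3 assessment points where 4 are collected, so the role and timing of the week-1 score are undefined

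*Protocol article*

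**What the plan says.** The Quantitative Analyses section models the four mechanism measures by analogy with the fidelity model, with one stated difference: "time will be treated as a categorical variable, reflecting the 3 assessment points rather than the 12 weekly sessions". The same section names patient demographics as covariates for all analyses and mentions no baseline mechanism score.

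The data collection is described differently:

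- Abstract, Methods: "Clinicians and patients will complete questionnaires at weeks 1, 5, 9, and 12".
- Participants and Procedures: "Clinicians and patients will complete questionnaires at 4 time points—baseline/week 1, week 5, week 9, and week 12".
- Participants and Procedures, clinician payments: "US $50 for week 1 and posttrial, US $25 for weeks 5 and 9".
- Table 2, Aim 3 secondary outcomes: each mechanism row is ticked at weeks 1, 5, 9 and Post.

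On timing, Participants and Procedures says "After obtaining informed consent, clinicians will be randomized to either the Tele-BE or Tele-AU condition" and calls the first survey baseline/week 1. It does not place that survey before or after allocation. Preliminary Analyses uses baseline variables for a randomisation check and plans a sensitivity analysis for imbalance.

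On scoring of attitudes, the Aim 3 Secondary Outcomes section says "Total scale scores will be computed by averaging all *z*-standardized items within each structural component", without naming the reference sample.

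**The concern.** Engagement of the target mechanisms is a stated part of aim 3, and this model is its quantitative test. With three time levels against four collected waves, two analysts could follow the article and fit different models, and those models differ in precision. With 15 clinicians per arm, the clinician's own starting score is likely to be among the most useful covariates available, and it is already being collected.

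The gain depends on timing. A week-1 score given before the clinician knows the arm is a clean covariate. One given after allocation or after a Tele-BE session may already carry part of the effect, and adjusting for it would then remove some of what the trial is looking for. It would also weaken the planned randomisation check. No later analysis can repair the order of survey and allocation, so it has to be fixed before aim 3 starts.

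**Working it through.** **Step 1: the count.** The article gives no power, effect size or SD for this analysis, so the figure to reproduce is the number of assessment points.

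- Listed time points: weeks 1, 5, 9, 12 = 4.
- Table 2 ticks per mechanism row: weeks 1, 5, 9, Post = 4.
- Clinician payments: 50 + 25 + 25 + 50 = US $150, the stated total, which covers 4 surveys.

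The figure of 3 is not reproduced. It fits the schedule only if one wave is not an outcome, and the obvious candidate is week 1. Table 2 puts the last clinician survey under Post where the text says week 12; the count is 4 either way.

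**Step 2: what each reading implies.** Assumptions, none of them from the article: outcome SD 1, equal correlation r between any two waves, complete data. From the article: n = 15 per arm. The SE of the arm difference at the last visit is sqrt(2v/n).

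- Week 1 unused: v = 1, SE = sqrt(2/15) = 0.365.
- Week 1 as covariate: v = 1 − r².
- Four waves, free mean per arm at every wave: generalised least squares gives 0.365 at each r below, so there is no gain.
- Four waves, common baseline mean: generalised least squares gives the same SE as the covariate model.

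| r (assumed) | 1 − r² | SE, week 1 unused or free means | SE, covariate or common baseline mean | SE reduction |
|---|---|---|---|---|
| 0.3 | 0.91 | 0.365 | 0.348 | 5% |
| 0.5 | 0.75 | 0.365 | 0.316 | 13% |
| 0.7 | 0.51 | 0.365 | 0.261 | 29% |
| 0.8 | 0.36 | 0.365 | 0.219 | 40% |

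With the anticipated 20% clinician dropout (12 per arm), the SE without baseline is 0.408 and the adjusted values are 0.389, 0.354, 0.292 and 0.245. The percentage reductions are the same. These figures ignore the small cost of estimating the covariate slope, so the 5% at r = 0.3 is slightly optimistic.

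In counts, four waves give up to 30 × 4 = 120 clinician assessments and three give 30 × 3 = 90. If week 1 really were unused, a quarter of the data would play no part in the model.

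**Step 3: why timing matters.** If allocation had already shifted week-1 scores by s, adjusting for them would understate the later effect by about r × s. For an illustrative s of 0.3 SD (assumed), that is 0.3 × 0.5 = 0.15 SD to 0.3 × 0.7 = 0.21 SD. This and the gain in step 2 rest on opposite premises and cannot both apply: the gain is clean only when the survey precedes allocation.

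**Step 4: what the article shows about timing.** Table 2 ticks session fidelity in the same week-1 column. It also ticks the acceptability, feasibility and usability scales there, which the Aim 4 Primary Outcomes section presents as measures of Tele-BE. That suggests week 1 could follow first use. In the other direction, the survey is labelled baseline and baseline variables serve as a randomisation check. The order is not settled.

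**Step 5: attitude scoring.** If items were standardised within each wave across both arms, every wave's overall mean would be 0 and the pooled time trend would vanish. Differences between arms would remain, in SD units of that wave.

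**The case against.** The strongest defence is that three simply means the three post-baseline waves. The first survey is called baseline, and the natural partner of such a model is adjustment for it. A full covariate list is normally left to the statistical analysis plan, which is not at hand. This stands to a degree: a reader might infer that a wave is dropped, that data are lost or that baseline is not adjusted for, and the article says none of these. Losing the final wave has least support, since Table 2 ticks it and clinicians are paid for it. But the article does not state the benign reading either. The fidelity model it points to treats all 12 sessions, the first included, as outcomes, and the covariate sentence it does give names only patient demographics.

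A reader might also infer that the week-1 survey follows randomisation because it is described later in the same paragraph. Order of sentences is not a schedule, so the supportable statement is that the timing is unclear.

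Likewise, the article does not say that attitudes are standardised wave by wave, and the reference sample is ordinary analysis-plan detail.

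Finally, little turns on this model. Mechanisms are secondary outcomes in a pilot, and the Progression Criteria use acceptability and feasibility scores, rated fidelity and qualitatively assessed motivation, not these survey scores. That is correct and limits the weight of the point.

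**Conclusion.** The contradiction is certain: three assessment points in the analysis text against four in the abstract, the procedures, Table 2 and the payments. It leaves the role of the week-1 mechanism score undefined, and the baseline/week 1 label leaves its timing undefined.

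The cost is conditional. It is zero if week-1 adjustment, or a common baseline mean, is already intended. Otherwise the last-visit SE is larger than it need be, and proper use of week 1 would cut it by about 5% to 40% over assumed correlations of 0.3 to 0.8. That range also assumes a survey completed before the clinician knows the arm. The documents do not support the stronger claim that precision is in fact being thrown away. This is worth correcting because it is nearly free, but it affects secondary pilot outcomes only.

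**What to change.** 1. Reconcile the count in Quantitative Analyses with the schedule by stating one model. Either model weeks 5, 9 and 12/Post with arm, wave, arm-by-wave and the week-1 score of the same measure as covariate, or model all four waves with a common baseline mean for the two arms. Both give the same precision for the last-visit comparison under the assumptions above.
2. State that clinicians complete the intention, attitude, norm and self-efficacy survey after consent and before they learn their allocation. The acceptability, feasibility and usability scales can stay after first use of the platform.
3. Minor: if attitude items are z-standardised, use one fixed reference for all waves, the pooled baseline mean and SD.

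The cost is a few sentences in the analysis plan and moving one existing survey slightly earlier. No measure, visit or participant is added. If baseline adjustment and a pre-allocation survey are already planned, only the wording changes.
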